### 10.1 Baseline Summary

Descriptive analyses of baseline characteristics detailed in section 8.1.3 will be carried out on the Intention-to-treat, Efficacy analysis and Partial compliance sets. Where deemed relevant, analyses will also be executed within selected subsets of these analysis sets. Specific subsets will be listed within the Statistical Analysis Plan. Results will be presented in tables where possible. Where percentages are to be calculated, the number of subjects in the condition within the specified analysis (sub)set will be used as the denominator. To assess whether differences between groups are statistically significant, paired or unpaired (depending on between or within group comparisons) two-sample t-tests and chi-squared tests will be used where appropriate.

### 10.2 Primary Analysis of Primary Endpoint(s)

The primary analysis of the primary endpoint will compare the performance of the algorithm applied in each study condition to detect if subjects were ever infected during Period 2. This analysis will be performed on both the Intention-to-treat and Efficacy analysis sets, within each period and stratified per risk group. For the subjects within each study condition, the daily prediction of possible SARS-CoV-2 infection and the results of PCR/antigen and serology tests will be summarized over the whole period per subject to determine (1) if a subject was ever judged to have a high risk for a potential SARS-Cov-2 infection (i.e. received a red-light indicator from the Ava COVID-RED app), and (2) if a subject was ever confirmed to have a SARS-CoV-2 infection by PCR/antigen or serology testing. For this comparison, parameters such as sensitivity, specificity, positive predictive value, and negative predictive value will be calculated.

To confirm whether a subject was ever infected in Period 2 with SARS-CoV-2, the serology status at the end of Period 2 for each subject still alive at that time will be used as the gold standard. Those with a previous positive test result will be excluded from the analysis. For subjects not alive at the end of Period 2, the status of available SARS-CoV-2 virus tests during Period 2 will be used (positive at any time) and for those without any test results, a physician diagnosis during Period 2 will be accepted provided there was a supportive lung CT scan used. All other subjects will be summarized for transparency but excluded from the estimation for sensitivity, specificity, positive predictive value and negative predictive value.

The following quantities are needed for these statistics:

- **Predicted condition positive:** The total number of subjects that obtained a red-light indicator from the Ava COVID-RED app at least once during Period 2.
- **Predicted condition negative:** The total number of subjects that never obtained a red-light indicator from the Ava COVID-RED app during Period 2.
- **Condition positive:** The total number of subjects who tested positive at least once using SARS-CoV-2 virus testing during Period 2 OR who had a positive serology test at the end of Period 2.
- **Condition negative:** The total number of subjects who never tested positive for the SARS-CoV-2 virus during Period 2 AND who had a negative serology test at the end of Period 2.

To compare cell counts between the two study conditions, log-linear modelling will be used which can take into account multiple factors that may be considered for inclusion in the model, which are further detailed in the SAP. A within-person (*de jure*) comparison will also be made by retrospectively evaluating the performance of the fully developed algorithm with and without the bracelet data included for all subjects. In this case, the sensitivity and specificity statistics will be compared using a McNemar's test. Statistical analyses will also be performed on data from both Periods 1 and 2 combined. See Section 10.4 for details on this analysis.

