#### **8.4.8 Collection & testing of plasma/blood sample**

Subjects will be asked to self-collect a capillary blood sample using provided materials at Baseline as well as upon completion of the Learning Phase, Period 1 and Period 2 by fingerprick for up to a total of 4 samples during the study. Subjects entering the study at the end of the recruitment Period will have a total of 3 samples, they will be asked to self-collect a sample at Baseline as well as upon completion of the Period 1 and Period 2.

Subjects will be requested to send the sample to the central laboratory within 24 hours using provided, pre-addressed medical envelopes with prepaid postage. The samples will be processed and stored at the central laboratory on the day of receipt. All samples collected at the end of the Learning Phase, and Period 2 will directly be tested for SARS-CoV-2 antibodies using an in-house ELISA method upon receipt. By testing at the end of each stage of the study, we have nearly 100% knowledge of infection status at the end of each trial period, thereby allowing assessment of sensitivity and specificity. Baseline samples will only be analyzed if the sample collected at the end of the Learning Phase is positive for SARS-CoV-2 antibodies or if the subject entered the study at the end of the recruitment Period. Samples collected at the end of Period 1 will only be analyzed if the sample collected at the end of Period 2 is positive for SARS-CoV-2 antibodies. In this way, subjects who had a SARS-CoV-2 infection prior to participation in the study or at start of Period 2 can be identified. The central laboratory in-house ELISA method assesses total SARS-CoV-2 antibodies (Ab), and if positive, isotype-specific (IgM and IgG) SARS-CoV-2 antibodies. Note that anti-S antibody serology tests will be used for baseline and Learning Phase samples. Anti-N antibody serology tests will be used for the Period 1 and Period 2 samples. Subjects will be informed on their testing result for SARS-CoV-2 antibodies.

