### 10.5 Analysis of Secondary Endpoint(s)

Secondary study endpoints mentioned in section 8.1.2 will be analysed and compared within the Intention-to-treat, Efficacy analysis and Partial compliance sets within each period. Where deemed relevant, analyses will also be executed within selected subsets of these analysis sets. Specific subsets will be listed within the Statistical Analysis Plan. Results will be presented in tables where possible. Where percentages are to be calculated, the number of subjects in the condition within the specified analysis (sub)set will be used as the denominator.

Where assumptions are met, Cochran-Mantel-Haenszel tests stratified by the risk strata will be performed in each period for multiple secondary endpoints, including:

- The number and percentage of subjects that obtained a red-light indicator by the applied algorithm at least once.
- The number and percentage of subjects with at least one positive SARS-CoV-2 virus test result during follow-up.

- The number and percentage of subjects that donated a blood sample for a SARS-CoV-2 antibody test at baseline, after the Learning Phase and after both periods.
- The number and percentage of subjects with a positive SARS-CoV-2 antibody test at baseline, after the Learning Phase and after both periods.
- The number and percentage of subjects with at least one positive SARS-CoV-2 virus test result during each period OR a positive SARS-CoV-2 antibody test result within those periods.
- The number and percentage of subjects without a positive SARS-CoV-2 virus test result during each period AND a negative SARS-CoV-2 antibody test result within those periods.
- The number and percentage of subjects that have reported experiencing each of the symptoms listed in the Ava COVID-RED app at least for one day during the study.
- The number and percentage of subjects that have reported experiencing each of the symptoms corresponding by the RIVM guidelines at least for one day during the study.
- The number of subjects who reported a positive SARS-CoV-2 virus test during the study and the percentage of subjects who reported a positive SARS-CoV-2 virus test during the study, with the number of subjects ever receiving a PCR test during the study as the denominator.

Where assumptions are met, t-tests will be performed in each period for multiple secondary endpoints, including:

- The average and median number of times a single subject obtained a red-light indicator by the applied algorithm.

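### Section 10.2 gives two incompatible rules for living subjects without an end-of-Period-2 sample; one of them inflates PPV and probably sensitivity

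*Protocol*

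**What the plan says.** Protocol section 10.2 sets out who counts as infected in Period 2 in two places.

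- **The text.** For living subjects, "the serology status at the end of Period 2 for each subject still alive at that time will be used as the gold standard". Virus tests serve as the reference only for subjects who died, with a CT-supported physician diagnosis as a further fallback for those without test results. Everyone else is described but left out of sensitivity, specificity, PPV and NPV.
- **The definitions for the 2x2 table.** Condition positive covers subjects "who tested positive at least once using SARS-CoV-2 virus testing during Period 2 OR who had a positive serology test". Condition negative is "The total number of subjects who never tested positive for the SARS-CoV-2 virus during Period 2 AND who had a negative serology test". In each, the serology meant is that of the sample closing Period 2.

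Section 10.5 repeats the second pattern among its secondary endpoints, for example "The number and percentage of subjects without a positive SARS-CoV-2 virus test result during each period AND a negative SARS-CoV-2 antibody test result". Section 8.4.8 expects almost complete information: "we have nearly 100% knowledge of infection status at the end of each trial period". The protocol gives no expected return rate for the samples.

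**The concern.** The text and the definitions disagree about a living subject who returns no end-of-Period-2 sample but had a positive virus test. The text excludes that subject and the definitions count the subject as infected. Section 10.2 does not say which prevails, and an analyst who codes the table from the definitions gets the asymmetric version.

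That version matters because inclusion then depends on the outcome and, through testing behaviour, on the index test. A red light directs the subject to virus testing (sections 3.5 and 8.4.12). Infected non-returners who were flagged are therefore likelier to be kept than those who were not, and uninfected living non-returners are never kept. This is partial verification acting on the primary accuracy estimates.

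The contrast between conditions could also move. Control red lights follow RIVM symptoms (section 3.3), which are also the criteria for GGD testing (section 3.5). A bracelet-only alert may be refused by the GGD and then needs a requested, mailed kit (sections 1.4 and 8.4.12), so the share of infected subjects with a confirmed test after an alert could differ by condition.

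Some missing samples should be expected. They are self-collected and posted, subjects may leave at any time, and the general approach in section 10 itself foresees missing data because the study is remote.

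**Working it through.** The protocol gives no figure that depends on this rule, so there is none to reproduce. The check computes the expected 2x2 cells under each rule.

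**Inputs (all assumed).**
- p = 5% infected. Table 2 of section 4.4 gives test positivity from 5,427/180,182 = 3.0% to 23,264/223,274 = 10.4%.
- S = 70% true sensitivity.
- F = 20% of uninfected subjects with a red light.
- m = share without an end sample, unrelated to infection or red light.
- t = 70% and u = 10%: chance that an infected subject has a positive virus test, with and without a red light.
- Serology is taken as perfect.

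**Cells under the definitions.**
- TP = p·S·[(1−m) + m·t]
- FN = p·(1−S)·[(1−m) + m·u]
- FP = (1−p)·F·(1−m)
- TN = (1−p)·(1−F)·(1−m)

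**At m = 20%.**
- TP = 0.035 × 0.94 = 0.0329
- FN = 0.015 × 0.82 = 0.0123
- FP = 0.95 × 0.20 × 0.80 = 0.152
- TN = 0.95 × 0.80 × 0.80 = 0.608
- Sensitivity = 0.0329/0.0452 = 72.8% (true 70.0%)
- PPV = 0.0329/0.1849 = 17.8% (true 0.035/0.225 = 15.6%)
- Specificity = 0.608/0.760 = 80.0%, unchanged
- NPV = 0.608/0.6203 = 98.0% (true 98.1%)

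| Missing | Sensitivity | PPV |
|---|---|---|
| 0% | 70.0% | 15.6% |
| 5% | 70.6% | 16.0% |
| 10% | 71.3% | 16.6% |
| 20% | 72.8% | 17.8% |
| 30% | 74.4% | 19.3% |

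**Under the text's exclusion rule**, all four cells are multiplied by (1−m). With the same missingness assumption, every measure equals its true value.

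**Other inputs.** With p = 10.4%, specificity 60%, t = 80%, u = 10% and m = 20%, sensitivity is 73.2% (true 70%) and PPV is 19.6% (true 16.9%). If testing does not depend on the red light (t = u = 50%), sensitivity is unbiased at 70.0%, but PPV is still 18.6%. The PPV bias therefore does not need the red-light link, while the sensitivity bias does.

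**Contrast between conditions.** Take control S = 70% and experimental S = 75.5%, a true difference of 5.5 points, with p and u as in the first set of inputs.
- Yields t = 70% (control) and 50% (experimental), m = 20%: experimental TP = 0.03775 × 0.90 = 0.033975 and FN = 0.01225 × 0.82 = 0.010045, so sensitivity is 77.2%. The difference is 77.2 − 72.8 = 4.4 points. At m = 5% it is 5.24 points.
- Yields reversed (50% control, 70% experimental), m = 20%: control 0.0315/0.0438 = 71.9%, experimental 0.035485/0.04553 = 77.9%. The difference is 6.0 points.
- Equal yields (70% in both): 5.42 points at m = 5% and 77.94 − 72.79 = 5.15 at m = 20%. The sensitivity odds are multiplied by the same factor in both conditions, so no difference appears where none exists, and a real one shrinks slightly on the percentage scale.

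**Incidence.** Section 10.5 divides by all subjects in the condition within the analysis set. At m = 20% that gives TP + FN = 4.5% against a true 5.0%. Dividing by classified subjects only would give 0.0452/0.8052 = 5.6%.

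**The case against.** The strongest reply is that the text of 10.2 governs. It excludes living subjects without serology whatever their virus tests, and on that rule the asymmetry does not arise. Section 8.4.8 expects almost complete status, mailed kits are offered to subjects whom the GGD turns away, and missing-data methods may properly be left to the statistical analysis plan.

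Much of this stands. It does not settle the matter, because the definitions are introduced as the quantities needed for the statistics and they contradict the text. The primary objective and the endpoint definition in 8.1.1 also accept PCR/antigen results as confirmation, so the definitions are not a stray reading. The near-complete status in 8.4.8 is an expectation with no return rate behind it. The exclusion rule is itself unbiased only if sample return is unrelated to infection and red light.

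A reader might infer several stronger points that the document does not support:
- **That the plan as a whole overstates accuracy.** Only one of its two rules does so.
- **That incidence is overstated.** With the denominator in 10.5, missing samples understate it.
- **That a subject without a sample can never count as uninfected.** Subjects who died have their own virus-test route in the text.
- **That the infections kept are mostly those after a red light.** The pathway makes this plausible, but no figure is given, and close contacts can be tested without symptoms (section 3.5).
- **That the contrast is biased against the bracelet.** Size and direction both depend on assumed yields.

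**Conclusion.** The point holds as a contradiction within section 10.2 that affects the primary accuracy estimates and should be resolved. If the definitions are followed, PPV is overstated whenever living non-returners have positive virus tests. Sensitivity is overstated when infected subjects with a red light are likelier to have a positive test. Specificity is unaffected and NPV falls very slightly.

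Under the first set of assumptions the sensitivity bias is 0.6 points at 5% missing and 2.8 points at 20%; PPV rises by 2.2 points at 20%. The contrast is materially affected only if test yield after an alert differs by condition: a true 5.5 points becomes about 5.2 at 5% missing or 4.4 at 20%, with yields of 70% and 50%, and the shift reverses if the yields do. If nearly all samples come back, the effect is small. None of the rates behind these figures is stated in the protocol.

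**What to change.** In 10.2, reconcile the text and the definitions with one evaluability rule that does not depend on the virus-test result:

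- A living subject enters the 2x2 table only with a usable end-of-Period-2 serology result. Among these, a positive virus test in Period 2 or positive serology is condition positive; all others are condition negative.
- Keep the existing rule for subjects who died, and word the condition-negative definition so that it allows for it.
- Report two sensitivity analyses: the unrestricted count under the present definitions, and an imputation or inverse-probability-weighted analysis for non-returned samples using red-light status, virus tests, symptoms, risk group, vaccination and compliance.
- Report sample return by condition and red-light status, so that the reader can judge how much the choice matters.

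This costs some rewording and modest extra analysis, with no new data. The main analysis loses a few virus-positive subjects without a sample, so intervals widen slightly. Imputation or weighting adds a missing-at-random assumption, which is why it belongs among the sensitivity analyses.

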In the Learning Phase and Period 1 of the study, versions of the algorithms will be applied that have been developed and trained using data accrued during an ongoing feasibility study in Liechtenstein (COVI GAPP study) and proprietary historical data from Ava Fertility Tracker bracelet users. These will be collectively referred to as the version 1 (V1) algorithms. Data collected during the Learning Phase of this study will be used to update and inform the algorithms which will then be implemented in Period 2. These versions of the algorithms will be collectively referred to as the version 2 (V2) algorithms. As such, Period 1 and 2 will evaluate different versions of the algorithms and provide insight into the possible improvement of the algorithms over time due to the increased availability of data for development. The applied version of the algorithms at different moments in the study will be taken into account during the statistical analysis. The final version of the algorithm (version 3; V3), which will be developed using all the data collected during the study, will also be applied retrospectively to all subjects, thereby enabling investigation of how the algorithm performed as compared to earlier versions. See Figure 2 for an illustration of this process.

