### *Development and validation of algorithms*

As indicated in section 3.3, the algorithms applied in both the control and experimental condition will continually be developed during the trial with specific versions being released and evaluated throughout. During the Learning Phase and Period 1, first versions of the algorithms will be implemented which have been developed using data collected from previous studies and existing users of the Ava bracelet. Data collected during the Learning Phase will then be used to develop second versions of the algorithms which will be

implemented and statistically evaluated in Period 2. When all subject follow-up is complete and all data is collected, final versions of the algorithms will be developed. As such, the Learning Phase will primarily be used to collect both physiological and symptom data to train both algorithms, Period 1 to gain further understanding of the first version of the algorithm and enable blinded sequences, and Period 2 will be used to statistically evaluate the second version of the algorithm as specified in the primary objective.

For these analyses, the duration of implementation of different versions of the algorithms will be taken into account. As such, the performance of the implemented algorithms will be calculated using data collected during its implementation. In addition, the performance of different versions of the algorithms can be assessed by applying them retrospectively to all of the collected raw data. In this way, the algorithms will be judged as actually implemented in the trial (*de facto* estimation) and under a hypothetical condition wherein the final developed algorithm is treated as having been implemented for each subject (*de jure* estimation).

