### 10.3 Secondary Analysis of Primary Endpoint(s)

The secondary analysis of the primary endpoint will compare which of the two algorithms between study conditions has superior performance characteristics for detecting early or asymptomatic SARS-CoV-2 indication or infection. Time-to-event analyses will be performed using the Intention-to-treat, Efficacy analysis and Partial compliance set. Analyses will be performed within each study period and stratified per risk group. Kaplan-Meier plots will be

constructed for visual support. An event will be defined as either the first indication (red-light indicator from the Ava COVID-RED app) or first infection (as confirmed by PCR/antigen testing) of SARS-CoV-2 of a subject during the study period. Subjects lost to follow-up or reaching the end of the period without infection will be censored. Stratified log-rank tests will be performed within each period to assess whether the experimental condition shows a statistically significant improvement (or lack thereof) in time to indication or infection as compared to the control condition with a median difference used to state the effect size. If the median is not yet reached in either study condition then a different quantile will be used. If other variables are to be taken into account, Cox proportional hazards models will be used where assumptions are met.

This same analysis will also be performed retrospectively in all subjects where the time to first indication or infection will be assessed using the algorithm based on only the symptoms data or both the symptoms and bracelet data within each subject. Because the measurement methods are correlated (both physically and in data collection), a within-person comparison can be made using paired statistical methods. If assumptions are satisfied, a Wilcoxon signed rank test will be used for this analysis; otherwise, other paired tests will be considered.

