## 10.7 Interim analysis

The applied algorithms in both study conditions will be updated using data gathered throughout the study and a new version will be implemented in Period 2 of the study. When evaluating the different versions of the algorithm as mentioned above, we will essentially obtain interim *de facto* estimates of the performance of these algorithms. The final version of the algorithm will also be retrospectively applied on the data of the subjects within the considered analysis sets to obtain a final *de jure* estimate of the performance. As this is not a traditional hypothesis testing study, there will not be any adjustments to the Type 1 error level (alpha) to account for any interim statistical analysis of trial data.

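### The retrospective within-person comparison scores the final (V3) algorithm on the data used to build it, so its McNemar p-values lean towards the bracelet version; the primary Period 2 comparison is not affected

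*Protocol*

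**What the plan says.** All references are to the protocol; the SAP was not available.

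- **What V3 is built from.** Section 3.3 describes a final version "which will be developed using all the data collected during the study, will also be applied retrospectively to all subjects".
- **When it is built.** Section 10 (Development and validation of algorithms): "When all subject follow-up is complete and all data is collected, final versions of the algorithms will be developed". The same section defines de jure estimation as judging the algorithms "under a hypothetical condition wherein the final developed algorithm is treated as having been implemented for each subject".
- **What it is scored on.** Section 10.7: "The final version of the algorithm will also be retrospectively applied on the data of the subjects within the considered analysis sets". The result is called the final de jure estimate of performance.
- **The paired tests.** Section 10.2 makes the within-person (de jure) comparison by "retrospectively evaluating the performance of the fully developed algorithm with and without the bracelet data included for all subjects", and "the sensitivity and specificity statistics will be compared using a McNemar's test". Section 10.3 adds: "This same analysis will also be performed retrospectively in all subjects where the time to first indication or infection will be assessed". There too the contrast is symptoms alone against symptoms plus bracelet in the same person, with a Wilcoxon signed rank test if its assumptions hold. Section 10.3 does not say which version is used.
- **The significance rule.** The general approach in Section 10 uses 0.05 two-sided or 0.025 one-sided and makes no exception for these comparisons.

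The primary analysis is separate. It compares the two conditions in Period 2 using the V2 algorithms, which are developed from Learning Phase data.

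**The concern.** A model scored on the data that trained it looks better than it will in new users, and the excess grows with the number of fitted inputs. The version with the bracelet contains everything the symptom version has plus the physiological inputs. Section 3.3 goes further and describes the control as deterministic rules, which have little to overfit. Sections 1.4 and 10 describe both algorithms as trained. In either case the version with the bracelet carries more optimism.

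McNemar's test assumes that the two classifiers were fixed independently of the outcomes being scored. Here they were not. The comparison could therefore report a significant gain for a bracelet that adds nothing. Sections 1.4 and 10 present the within-subject analysis as evidence of the bracelet's value over symptom reporting alone.

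**Working it through.** The protocol gives no figure for the de jure comparison. Tables 3 to 5 concern the between-condition Fisher and log-rank tests, so there is nothing to reproduce. The check has a textual part and an illustrative part.

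**1. Do development and evaluation data coincide?** Development data: everything collected in the study (3.3), after all follow-up (10). Evaluation data: all subjects (3.3, 10.2), or the subjects in the trial's own analysis sets (10.7). They coincide, and no later trial data remain for validation.

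**2. How many infected subjects?** The protocol powers its analyses on Table 2. Positives divided by tested:
- Week 36: 5,427 / 180,182 = 3.01%; × 20,000 = 602.
- Week 40: 23,264 / 223,274 = 10.42%; × 20,000 = 2,084.

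**3. How often would a useless bracelet win?** Assumptions not in the protocol: 20,000 subjects; one symptom score shifted by 1.5 SD in the infected; bracelet features that are pure noise; a linear classifier; both versions set to 90% specificity on the data; exact two-sided McNemar test at 0.05 in the infected. Only rejections favouring the bracelet are counted, so the nominal maximum is 0.025. In the 5-fold column the threshold was set in the training folds.

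| Infected | Noise features | Replicates | Same data: rejections | Same data: sensitivity gain (points) | 5-fold: rejections | 5-fold: gain (points) |
|---|---|---|---|---|---|---|
| 602 | 5 | 200 | 0.005 | 0.04 | 0.005 | −0.19 |
| 602 | 20 | 200 | 0.040 | 0.38 | 0.000 | −0.58 |
| 602 | 50 | 120 | 0.175 | 1.30 | 0.000 | −1.08 |
| 602 | 100 | 60 | 0.367 | 2.23 | 0.000 | −2.18 |
| 602 | 200 | 30 | 0.967 | 4.82 | 0.000 | −4.35 |
| 2,084 | 50 | 60 | 0.167 | 0.39 | 0.000 | −0.28 |

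A separate run, also with 20,000 subjects and matched at 90% specificity (60 replicates), gave 0.03, 0.18 and 0.40 for 20, 50 and 100 features with 602 infected. Monte Carlo error matters. For example, √(0.04 × 0.96 / 200) = 0.014, so 0.04 cannot be told apart from 0.025, whereas 0.175 has a standard error of √(0.175 × 0.825 / 120) = 0.035 and clearly exceeds it.

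**4. Is cross-fitting enough by itself?** Take a symptom rule that detects 70% of infections, and a noise score (30 features) that flags a further 5% of symptom-negative uninfected subjects. The apparent sensitivity gain was 3.3 points against 1.6 cross-fitted with 602 infected, and 2.3 against 1.5 with 2,084. Optimism is therefore 3.3 − 1.6 = 1.7 and 2.3 − 1.5 = 0.8 points. With 5 features it was 0.6 to 0.3 points over the same range.

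The cross-fitted remainder is chance flagging: 5% of the 30% missed = 1.5 points. In 602 infected that is about 9 extra detections against none lost, and exact McNemar gives p = 2 × 0.5⁹ = 0.004. When flags are only added, sensitivity tested alone rewards a useless bracelet even out of sample. Specificity has to be matched or compared jointly.

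**The case against.** - **The primary result does not rest on this.** This stands. A reader might infer that the trial's main conclusion is compromised. It is not, because the Period 2 comparison uses V2, which is not built from Period 2 data. The within-person comparison is supplementary, and Section 10 calls its setting hypothetical.
- **Cross-validation may be in the SAP.** It may, and silence about technique alone would be no finding. But the protocol does more than stay silent: it states the development data and the evaluation data, and they are the same. Followed as written, the rule gives resubstitution results.
- **The bias may be small.** This stands in part. Section 3.2 names three bracelet parameters and Section 1.4 names five. With a handful of linear terms the bias is negligible. Nightly signals can yield many derived features, and a machine-learning model may be more flexible than a linear one, but the protocol specifies neither and flexible learners were not simulated. A reader might infer optimism as large as the 4 to 5.5 point differences in Table 3. At the infection numbers implied by Table 2, 30 linear features give about 1 to 2 points.
- **The Wilcoxon test may use another version.** This stands. The link to V3 is inferred from the retrospective application in all subjects and the de jure definition.
- **This is not the only route to the bracelet's own contribution.** This also stands. Section 10 allows other versions to be applied retrospectively to the raw data, and secondary objective 4 addresses independent predictiveness.

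**Conclusion.** The point holds for the supplementary V3 results: the final de jure estimate and the within-person McNemar comparison, and probably the retrospective Wilcoxon comparison. As written they are apparent performance and lean towards the bracelet version, so their p-values are not valid evidence of added value.

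The direction follows from the protocol's own text. The size does not: it depends on feature count, model flexibility and number infected. Under the linear, pure-noise assumptions above, the false rejection rate runs from no inflation at 5 features to 15 or more times the nominal 0.025 at 100 (0.37 / 0.025 = 14.8; 0.40 / 0.025 = 16). The primary Period 2 comparison of the V2 algorithms stands.

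**What to change.** 1. In Sections 10.2, 10.3 and 10.7, state that V3 performance, and every paired test on V3, uses only subject-level cross-fitted predictions (nested cross-validation), with the alert threshold also set inside the training folds.
2. State that sensitivity and specificity are compared jointly, or that sensitivity is compared at matched specificity. Otherwise extra alerts alone can produce a gain.
3. Label any V3 result from the full-data fit as descriptive apparent performance, without a p-value.
4. Name the algorithm version used for the paired Wilcoxon comparison in Section 10.3.
5. Add an out-of-sample paired analysis: apply V2, frozen before Period 2, with and without bracelet data to all subjects' Period 2 data. Train the no-bracelet version by the same method on Learning Phase data. If the symptom rules of Section 3.3 serve as the no-bracelet version, the contrast mixes model type with bracelet data.

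Cost: no new data collection, since all subjects complete the diary and wear the bracelet throughout. It needs repeated model fitting for the cross-fitting and one additional trained model for item 5, and the V3 figures will look less favourable. It should be settled before V3 development begins, and item 5 before Period 2 data are examined.
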